## 3.4 Safety Measurements

### 3.4.1 Clinical and Laboratory Measurements for Safety

Eligible subjects who enroll in the long term follow-up after receiving GARDASIL™ vaccination series will be followed for (1) vaccine- or study procedure-related serious adverse experiences and (2) serious adverse experiences resulting in death (3) pre-specified medical conditions including, **but are not limited to,** incident cases of: systemic lupus erythematosus, rheumatoid arthritis, Guillain-Barre syndrome, acute disseminated encephalomyelitis and multiple sclerosis, and (4) pregnancy follow-up outcomes.

### 3.4.2 Recording Adverse Experiences

An adverse experience is defined as any unfavorable and unintended change in the structure, function, or chemistry of the body temporally associated with the use of the SPONSOR’s product, whether or not considered related to the use of the product. Any worsening (i.e., any clinically significant adverse change in frequency and/or intensity) of a preexisting condition which is temporally associated with the use of the SPONSOR’s product, is also an adverse experience.

Changes resulting from normal growth and development which do not vary significantly in frequency or severity from expected levels are not to be considered adverse experiences. Examples of this may include, but are not limited to, teething, typical crying in infants and children, and onset of menses or menopause occurring at a physiologically appropriate time.

The following safety measurements will be collected from the time the consent form is signed through the completion of the year-10 visit:

Serious Adverse Experiences (SAEs) (as defined in the detailed protocol) judged by the study investigator to be possibly, probably, or definitely related to prior administration of GARDASIL; Serious Adverse Experiences (as defined in the detailed protocol) judged by the study investigator to be possibly, probably, or definitely related to a study procedure; and Death of a study subject.

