## 1.7 Study Flow Chart

| Event/Test | Contact and Obtain Consent | Years following Base Study Day 1 visit (window for each visit is ± 6 months) | | |
| --- | --- | --- | --- | --- |
| 6 | 8 | 10 |
| Obtain informed consent | x |  |  |  |
| Review inclusion/exclusion criteria |  | x |  |  |
| Provide Participant Identification Card |  | x |  |  |
| Collect medical/gynecologic history † |  | x | x | x |
| Perform physical exam |  | x | x | x |
| Inspect external genital areas for warts/lesions‡ |  | x | x | x |
| Perform pelvic exam |  | x | x | x |
| Perform **optional** tests, as necessary§ |  | (x) | (x) | (x) |
| Perform Pap test (ThinPrep™) for cytology || |  | x | x | x |
| Inspect vaginal area for warts/lesions‡ |  | x | x | x |
| Perform bimanual exams |  | x | x | x |
| Collect blood (serum) for anti-HPV |  | x | x | x |
| Document clinical follow-up for safety ¶ |  | x | x | x |
| **Procedures must be conducted in the order provided within the study flow chart.**  Contact and consent may be obtained any time prior to procedures at Year 6 visit (including the day of year 6 visit). Visits for Year 6, Year 8 and Year 10 will be calculated from Day 1 of original study and visit window for each visit is +/- 6 months of actual time point.  † History will be updated as needed at these visits and at unscheduled visits.  ‡ The external genital wart/lesion exam must be conducted in 2 parts in order to limit contamination between anatomical areas. The external portion of the exam including vulvar, labia, perineum, perianal and other external areas will be performed prior to the pelvic exam. The vaginal portion of the wart/lesion inspection will be performed after the pelvic exam and all specimen collection is completed.  § HSV Culture may be performed if indicated. Vaginal pH, wet mount, whiff test, and KOH may be performed at the investigator's discretion.  || Cytology for Pap test to be performed by central laboratory selected by SPONSOR.  ¶ Serious adverse experiences, as defined in Section 3.4 will be collected for all subjects throughout the extension phase. All reports of pregnancy will be reported to the SPONSOR and followed to outcome. | | | | |

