### 2.1.1 Primary Safety

Objective: To observationally describe the general safety of a 3-dose regimen of GARDASIL™ [Human Papillomavirus (Types 6, 11, 16, 18) Recombinant Vaccine] in women 24 to 50 years of age during a period of 5 to 10 years following vaccine Dose 1 by describing vaccine- or study procedure-related SAEs, SAEs resulting in death and pre-specified medical conditions, and pregnancy follow-up outcomes.

Hypothesis: No hypothesis relating to safety will be tested.

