## 2.6 List of Safety Measurements

The following safety measurements will be collected:

- Serious Adverse Experiences (SAEs) (as defined in the detailed protocol) judged by the study investigator to be possibly, probably, or definitely related to prior administration of GARDASIL™
- SAEs (as defined in the detailed protocol) judged by the study investigator to be possibly, probably, or definitely related to a study procedure
- Death of a study subject

Safety outcomes as requested by regulatory agencies for each subject who has consented to this LTFU study and pregnancy outcome will also be collected during the follow-up period. Specific disorders will include **but are not limited to** incident cases of: systemic lupus erythematosus, rheumatoid arthritis, Guillain-Barre syndrome, acute disseminated encephalomyelitis and multiple sclerosis.

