### 3.4.5 Immediate Reporting of Adverse Experiences to the SPONSOR

#### 3.4.5.1 Serious Adverse Experiences

Serious adverse experiences that are considered by the investigator to be possibly, probably, or definitely related to a previous vaccination of GARDASIL, or serious adverse experiences considered by the investigator to be related to a study procedure, or death due to any cause, which occurs to any subject from the time the consent is signed through the 10-year final visit, must be reported within 24 hours to one of the individual(s) listed on the sponsor contact information page found in the Administrative Binder.

Additionally, any serious adverse experience brought to the attention of an investigator who is a qualified physician at any time outside of the time period specified in the previous paragraph also must be reported immediately to one of the individuals listed on the sponsor contact information page (found in the administrative binder) if the event is either:

1. A death which resulted in the subject/patient discontinuing the study

or

2. A serious adverse experience that is considered by an investigator who is a qualified physician to be possibly, probably, or definitely vaccine related.

3. A serious adverse experience that is considered by an investigator who is a qualified physician to be possibly, probably, or definitely protocol-specified procedure related.

All subjects/patients with serious adverse experiences must be followed up for outcome.

All subjects who become pregnant must be followed to the completion/termination of the pregnancy.

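### The list of collected safety data in Section 3.4.2 leaves out the pre-specified medical conditions that Sections 2.6 and 3.4.1 require, so sites may under-record part of the primary safety objective

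*Protocol*

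**What the plan says.** Section 2.1.1 sets out to describe related serious adverse experiences (SAEs) together with "SAEs resulting in death and pre-specified medical conditions, and pregnancy follow-up outcomes". It does not name the conditions.

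Section 2.6 first lists three measurements: vaccine-related SAEs, procedure-related SAEs, and death. It then adds: "Safety outcomes as requested by regulatory agencies for each subject who has consented to this LTFU study and pregnancy outcome will also be collected". The disorders it names are incident cases of "systemic lupus erythematosus, rheumatoid arthritis, Guillain-Barre syndrome, acute disseminated encephalomyelitis and multiple sclerosis", and the list is left open-ended. No seriousness or causality condition is attached.

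Section 3.4.1 says women are followed for four things. The conditions are an item of their own, separate from related SAEs and fatal SAEs: "2) serious adverse experiences resulting in death (3) pre-specified medical conditions including" the same five disorders. Pregnancy outcome is the fourth.

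Section 3.4.2 states what is collected between signed consent and the end of the Year 10 visit. It has three entries: SAEs "judged by the study investigator to be possibly, probably, or definitely related to prior administration of GARDASIL", SAEs related to a study procedure, and death.

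Section 3.4.5.1 requires 24-hour reporting of SAEs "possibly, probably, or definitely related to a previous vaccination of GARDASIL", procedure-related SAEs and death from any cause.

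The safety footnote to the flow chart (Section 1.7) reads: "Serious adverse experiences, as defined in Section 3.4 will be collected for all subjects throughout the extension phase". It then adds pregnancy. Section 2.4.1 likewise mentions only investigator-reported SAE data and pregnancy outcomes.

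**The concern.** The section headed for recording adverse experiences, which a site would naturally consult, does not contain one of the four things that 3.4.1 says women are followed for. The missing item belongs to the primary safety objective.

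The omission matters because of the design. Section 2.7 says there is no control group, and Section 3.2.3.4 says everyone involved knows that every participant was vaccinated. Safety is described and not tested, so the useful output for these disorders is a complete count of new cases whatever their presumed cause. If some sites apply the related-or-fatal scope of 3.4.2 and others the wider scope of 2.6 and 3.4.1, the count depends on which section was read. A small number could look reassuring when it partly reflects cases not written down. Outpatient diagnoses and onset dates are also harder to recover after Year 10.

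A second mismatch adds to the uncertainty. The flow-chart footnote and 2.4.1 speak of SAEs with no relatedness filter, while 3.4.2 filters every non-fatal SAE by relatedness.

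**Working it through.** There is no figure to reproduce and no arithmetic applies. The check sets the passages side by side.

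**Step 1. Take the four items of Section 3.4.1 and look for an operative rule for each.**

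| Item in 3.4.1 | Listed in 3.4.2 | In the 24-hour rule of 3.4.5.1 | Own rule elsewhere |
| --- | --- | --- | --- |
| (1) Vaccine- or procedure-related SAEs | Yes | Yes | Not needed |
| (2) Fatal SAEs | Yes, as any death | Yes, any cause | Not needed |
| (3) Pre-specified conditions | No | No | None found |
| (4) Pregnancy outcomes | No | No (3.4.5.1 only repeats follow-up to outcome) | Yes: 3.2.3.3.2, 3.4.4 and the flow-chart footnote |

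Three of the four items have an operative rule. Item (3) has none.

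**Step 2. Compare 3.4.2 with 2.6.** The three entries in 3.4.2 match the three bullets of 2.6. What 3.4.2 lacks is the paragraph that follows those bullets, which adds the regulator-requested outcomes and pregnancy. Pregnancy is restored elsewhere; the conditions are not. This pattern suggests a drafting omission, not a decision to narrow the scope.

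**Step 3. Trace one case.** Suppose a woman is diagnosed with rheumatoid arthritis as an outpatient between the Year 6 and Year 8 visits, and the investigator judges it unrelated and not serious.
- Under 2.6 and 3.4.1 she is an incident case to be collected and followed.
- Under 3.4.2 she matches none of the three entries.
- Under 3.4.5.1 nothing is due within 24 hours.
- At Year 8 her medical history is updated as needed. Section 3.2.3.3.1 sends the site to Section 3.4 as a whole, where 3.4.1 says to follow her and 3.4.2 does not list her.

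The same document therefore supports both recording and not recording her.

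**Step 4. Compare the SAE scope.** Take a non-fatal SAE judged unrelated to vaccine or procedure. Read at face value, the flow-chart footnote and 2.4.1 include it. Sections 2.6, 3.4.1 and 3.4.2 do not list it.

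**Step 5. Check the objective.** The phrase in 2.1.1 that joins fatal SAEs to the conditions can be read as limiting the conditions to serious events. Sections 2.6 and 3.4.1 show no such limit, so 2.1.1 does not settle the matter.

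**The case against.** A reader might go further and infer that these conditions enter the database only if they are serious and judged related to the vaccine. The documents do not support that, for these reasons:

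- Section 2.6 says in terms that these outcomes are collected, and 3.4.1 lists them separately from related SAEs. Neither applies a filter.
- The list in 3.4.2 does not claim to be complete. It also omits pregnancy, which is plainly collected, so silence there cannot mean exclusion.
- Section 3.4.5.1 governs expedited reporting. Absence from a 24-hour rule does not keep an event out of the database.
- Fatal cases are captured whatever the cause, serious procedure-related cases are captured, and some diagnoses could count as serious under the important-medical-event criterion of Table 3-3.
- Each scheduled visit includes a medical history and a safety follow-up that refers to Section 3.4, which opens with the named conditions. A site has a route to them.

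Two further points are fair. The footnote's reference to Section 3.4 can be read as adopting that section's scope, which would soften the SAE mismatch. Section 3.6 leaves data management procedures to the sponsor; they are not shown and may carry a recording instruction.

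All of this stands against the exclusion reading. It does not remove the inconsistency. The comparison with pregnancy works in both directions: it shows 3.4.2 is incomplete, but pregnancy has its own section and these conditions do not. A form supplied separately would not reconcile the protocol's own sections.

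**Conclusion.** The point holds as an inconsistency that risks under-recording, not as an exclusion by rule. Sections 2.6 and 3.4.1 require new cases of the five named disorders to be collected or followed regardless of seriousness or causality. Section 3.4.2 omits them, and no other section supplies a window, recording rule or reporting route. The SAE scope also differs between the flow-chart footnote and 2.4.1 on one side and 3.4.2 on the other, subject to how the footnote's cross-reference is read.

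The size is one of the four follow-up items in 3.4.1, and it belongs to the primary safety objective. The number of cases that might be missed cannot be derived: the documents give no background incidence for these disorders and no basis for the share an investigator would judge related. The conclusion needs neither figure. It assumes only that some sites will take the 3.4.2 list as their recording instruction and that the unseen sponsor procedures do not already correct it. The textual contradiction is certain; its practical effect depends on those two assumptions.

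**What to change.** 1. Add a fourth entry to the list in Section 3.4.2: any new diagnosis of a pre-specified medical condition named in 2.6 or 3.4.1, regardless of seriousness or judged causality, with its onset date. State that it is asked about at the Year 6, 8 and 10 medical histories.
2. Reconcile the SAE scope in the flow-chart footnote and Section 2.4.1 with 3.4.1 and 3.4.2, so that one scope is stated throughout.
3. In Section 3.4.5.1, add a cross-reference to the new entry. The expedited rule need not be widened.

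Two additions are optional: closing the list of conditions, which is called pre-specified but left open-ended, and reporting counts per person-year by cohort. The correction does not depend on either.

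The cost is protocol wording and slightly more data entry at three visits where a history is already taken. More cases may be recorded, which is the purpose.

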### 3.4.3 Definition of an Overdose for This Protocol

No vaccination will be provided in the long term follow-up and therefore no definition of overdose is associated with this protocol. However, if an investigator discovers that a subject received an additional dose of GARDASIL™ outside the context of the study, this should be reported to the sponsor.

#### 3.4.3.1 Reporting of Overdose to SPONSOR

If an adverse experience(s) is associated with (“results from”) the overdose of test drug or vaccine, the adverse experience(s) is reported as a serious adverse experience, even if no other criteria for serious are met.

If a dose of test drug or vaccine meeting the protocol definition of overdose is taken without any associated clinical symptoms or abnormal laboratory results, the overdose is reported as a non-serious Event of Clinical Interest (ECI), using the terminology “accidental or intentional overdose without adverse effect.”

All reports of overdose with and without an adverse experience must be reported within 24 hours to one of the individuals listed on the sponsor contact information page found in the Administrative Binder.

### 3.4.4 Reporting of Pregnancy to SPONSOR

Although not considered an adverse experience, it is the responsibility of investigators or their designees to report any pregnancy in a subject/patient (spontaneously reported to them) which occurs during the study or within 14 days of completing the study. All subjects/patients who become pregnant must be followed to the completion/termination of the pregnancy. If the pregnancy continues to term, the outcome (health of infant) must also be reported to one of the individuals listed on the SPONSOR Contact Information page found in the Administrative Binder.

### 3.4.5 Immediate Reporting of Adverse Experiences to the SPONSOR

#### 3.4.5.1 Serious Adverse Experiences

Serious adverse experiences that are considered by the investigator to be possibly, probably, or definitely related to a previous vaccination of GARDASIL, or serious adverse experiences considered by the investigator to be related to a study procedure, or death due to any cause, which occurs to any subject from the time the consent is signed through the 10-year final visit, must be reported within 24 hours to one of the individual(s) listed on the sponsor contact information page found in the Administrative Binder.

Additionally, any serious adverse experience brought to the attention of an investigator who is a qualified physician at any time outside of the time period specified in the previous paragraph also must be reported immediately to one of the individuals listed on the sponsor contact information page (found in the administrative binder) if the event is either:

1. A death which resulted in the subject/patient discontinuing the study

or

2. A serious adverse experience that is considered by an investigator who is a qualified physician to be possibly, probably, or definitely vaccine related.

3. A serious adverse experience that is considered by an investigator who is a qualified physician to be possibly, probably, or definitely protocol-specified procedure related.

All subjects/patients with serious adverse experiences must be followed up for outcome.

All subjects who become pregnant must be followed to the completion/termination of the pregnancy.

### 3.4.6 Evaluating Adverse Experiences

Refer to Table 3-3 for instructions in evaluating adverse experiences.

Table 3-3

An investigator who is a qualified physician, will evaluate all adverse experiences as to:

| **Maximum** | **Mild** | awareness of sign or symptom, but easily tolerated (for pediatric studies, awareness of symptom, but easily tolerated) |
| --- | --- | --- |
| **Intensity** | **Moderate** | discomfort enough to cause interference with usual activity (for pediatric studies, definitely acting like something is wrong) |
|  | **Severe** | incapacitating with inability to work or do usual activity (for pediatric studies, extremely distressed or unable to do usual activities) **Injection site redness or swelling from the day of vaccination through Day 4 post-vacc will be evaluated by maximum size.** |
| **Seriousness** | A serious adverse experience is any adverse experience occurring at any dose that: | |
|  | **†Results in death; or** | |
|  | †**Is life threatening; or** places the subject/patient, in the view of the investigator, at immediate risk of death from the experience as it occurred [Note: This does not include an adverse experience that, had it occurred in a more severe form, might have caused death.]; or | |
|  | **†Results in a persistent or significant disability/incapacity** (substantial disruption of one’s ability to conduct normal life functions); or | |
|  | †**Results in or prolongs an existing inpatient hospitalization** (hospitalization is defined as an inpatient admission, regardless of length of stay, even if the hospitalization is a precautionary measure for continued observation.) (Note: Hospitalization [including hospitalization for an elective procedure] for a preexisting condition which has not worsened does not constitute a serious adverse experience.); or | |
|  | †**Is a congenital anomaly/birth defect** (in offspring of subject/patient taking the product regardless of time to diagnosis); or | |
|  | **Is a cancer; or** | |
|  | **Is an overdose** (Whether accidental or intentional.) Any overdose whether or not associated with an adverse experience must be reported within 24 hours. | |
|  | **Other important medical events** that may not result in death, not be life threatening, or not require hospitalization may be considered a serious adverse experience when, based upon appropriate medical judgment, the event may jeopardize the subject/patient and may require medical or surgical intervention to prevent one of the outcomes listed previously (designated above by a †). | |
| **Duration** | Record the start and stop dates of the adverse experience. If less than 1 day, indicate the appropriate length of time and units | |
| **Action taken** | Did the adverse experience cause the test vaccine to be discontinued? | |
| **Relationship to test vaccine** | Did the test vaccine cause the adverse experience? The determination of the likelihood that the test vaccine caused the adverse experience will be provided by an investigator who is a qualified physician. The investigator’s signed/dated initials on the source document or worksheet, that supports the causality noted on the AE form, ensures that a medically qualified assessment of causality was done. This initialed document must be retained for the required regulatory time frame. The criteria below are intended as reference guidelines to assist the investigator in assessing the likelihood of a relationship between the test vaccine and the adverse experience based upon the available information.  **The following components are to be used to assess the relationship between the test vaccine and the AE;** the greater the correlation with the components and their respective elements (in number and/or intensity), the more likely the test vaccine caused the adverse experience (AE): | |
|  | **Exposure** | Is there evidence that the subject/patient was actually exposed to the test vaccine such as: reliable history, acceptable compliance assessment (e.g. diary), seroconversion or identification of vaccine virus in bodily specimen? |
|  | **Time Course** | Did the AE follow in a reasonable temporal sequence from administration of the test vaccine?  Is the time of onset of the AE compatible with a vaccine-induced effect? |
|  | **Likely Cause** | Is the AE not reasonably explained by another etiology such as underlying disease, other drug(s)/vaccine(s), or other host or environmental factors |
| **Relationship** | **The following components are to be used to assess the relationship between the test vaccine and the AE: (continued)** | |
| **to test vaccine** | **Dechallenge** | (not applicable for vaccines) |
| **(continued)** | **Rechallenge** | Was the subject/patient reexposed to the test vaccine in this study?  If yes, did the AE recur or worsen?  If yes, this is a positive rechallenge. If no, this is a negative rechallenge.  (Note: This criterion is not applicable if: (1) the initial AE resulted in death or permanent disability, or (2) the study is a single-dose vaccine study.) NOTE: IF A RECHALLENGE IS PLANNED FOR AN ADVERSE EVENT WHICH WAS SERIOUS AND WHICH MAY HAVE BEEN CAUSED BY THE TEST VACCINE, OR IF REEXPOSURE TO THE TEST VACCINE POSES ADDITIONAL POTENTIAL SIGNIFICANT RISK TO THE SUBJECT/PATIENT, THEN THE RECHALLENGE MUST BE APPROVED IN ADVANCE BY THE U.S. CLINICAL MONITOR AND THE INSTITUTIONAL REVIEW BOARD/INDEPENDENT ETHICS COMMITTEE. |
|  | **Consistency with Study Vaccine Profile** | Is the clinical/pathological presentation of the AE consistent with previous knowledge regarding the test vaccine or vaccine class pharmacology or toxicology? |
| The assessment of relationship will be reported on the case report forms /worksheets by an investigator who is a qualified physician according to his/her best clinical judgment, including consideration of the above elements. | | |
| **Record one of the following:** | | **Use the following scale of criteria as guidance (not all criteria must be present to be indicative of a vaccine relationship).** |
| **Yes, there is a reasonable possibility of vaccine relationship.** | | There is evidence of exposure to the test vaccine. The temporal sequence of the AE onset relative to the administration of the test vaccine is reasonable. The AE is more likely explained by the test vaccine than by another cause.  **Depending on data collection method employed, vaccine relationship may be further graded as follows:** |
|  | **Definitely related** | There is evidence of exposure to the test vaccine. The temporal sequence of the AE onset relative to administration of the test vaccine is reasonable. The AE is more likely explained by the test vaccine than by another cause. Dechallenge is positive. Rechallenge (if feasible) is positive. The AE shows a pattern consistent with previous knowledge of the test vaccine or test vaccine class. |
|  | **Probably related** | There is evidence of exposure to the test vaccine. The temporal sequence of the AE onset relative to administration of the test vaccine is reasonable. The AE is more likely explained by the test vaccine than by another cause. Dechallenge (if performed) is positive. |
|  | **Possibly related** | There is evidence of exposure to the test vaccine. The temporal sequence of the AE onset relative to administration of the test vaccine is reasonable. The AE could have been due to another equally likely cause. Dechallenge (if performed) is positive. |
| **No, there is not a reasonable possibility of vaccine relationship** | | Subject did not receive the test vaccine OR temporal sequence of the AE onset relative to administration of the test vaccine is not reasonable OR there is another obvious cause of the AE. (Also entered for a subject with overdose without an associated AE.)  **Depending on data collection method employed, vaccine relationship may be further graded as follows:** |
|  | **Probably not related** | There is evidence of exposure to the test vaccine. There is another more likely cause of the AE. Dechallenge (if performed) is negative or ambiguous. Rechallenge (if performed) is negative or ambiguous. |
|  | **Definitely not related** | The subject/patient did not receive the test vaccine. **OR** Temporal sequence of the AE onset relative to administration of the test vaccine is not reasonable. OR There is another obvious cause of the AE. |

